
**Fig. 3 Fig3:**
[figure not shown]
The baseline population duration of high flow nasal cannula (HFNC) and simulated duration with an intervention effect size of a median duration 6.08 h less than baseline (hazard ratio [HR] 1.27; gold line and numbers in table) and with an intervention effect size of a median duration 1.7 h less than baseline (hazard ratio [HR] 1.7; pink line and numbers in table)

**Fig. 4 Fig4:**
[figure not shown]
Results of trial simulations: **A** the proportion of trial conclusions at 3 interim analyses and 1 final analysis deemed futile (red), inconclusive (gray), intervention promising (light blue), and intervention superior (dark blue). Trial simulations indicate that by assuming a true hazard ratio effect size of 1.27, equivalent to a 6-h reduction in the median duration of HHFNC, and enrolling a maximum of 350 children, there will be a > 0.75 probability of declaring superiority (interim analysis posterior probability > 0.99 or final analysis posterior probability > 0.9) and a > 0.85 probability of declaring superiority or the CDS intervention showing promise (posterior probability of > 0.8); **B** distribution of total duration of the trials in simulations; **C** distribution of total enrollment in simulations

### Monitoring and ensuring compliance

REST EEC is a pragmatic trial embedded within real world workflows and relies on minimal infrastructure components that would be typical in a traditional trial, such as research coordinators tracking compliance with an assigned study intervention. Trial oversight and the steering committee consist of members of relevant hospital operations teams. This includes clinical intensivist leadership, physician informaticians, nurse informaticians, and nurse improvement specialists. Summary enrollment data are emailed and reviewed weekly by a physician informatician and 2 nurse informaticians. To ensure adoption of the “HFNC for Bronchiolitis” order and ongoing adherence to the study workflow, the trial relies on CHP QI resources to support its ongoing conduct. Nurse clinician educators and physician faculty clinical leaders in the emergency department and PICU informed their respective workforces about the trial design and expectations for frontline clinicians. As QI methods emphasize the importance of patient engagement and clinician feedback, the REST EEC trial was integrated into existing patient and clinician QI structures at the study site. Upon admission, a bedside nurse educates all patient caregivers on the caregivers’ ability to advocate and intervene in patient care. This includes questioning care team decisions, including the decision to wean HFNC, as well as calling a “Condition Help” if a parent feels unheard about a patient safety concern. The trial has been iteratively reviewed in PICU physician quality reporting system (PQRS) sessions that serve as the main forum for introducing and updating the PICU physician faculty on the progress of QI initiatives. Biannual updates on trial progress are planned for PQRS sessions, during which time an open forum for discussion and feedback from physicians, nurses, respiratory therapists, pharmacists, and social workers will occur. The PICU QI forum, an in-hospital safety event reporting system, as well as ad hoc communication to PICU clinical leadership, will be used to collect reports of unintended effects of trial interventions or conduct. Assessment and management of any reports of unintended, adverse effects will be handled by the PICU clinical leadership in communication with the REST EEC study team. The data collection strategies are the same used to track progress of other inpatient CHP performance improvement initiatives and are performed by a quality improvement data team at UPMC. This team includes nurse informaticians, a physician informatician who also serves as the study principal investigator, a data analyst, a project manager, and a nurse quality improvement specialist. Iterative plan-do-study-act (PDSA) cycles are used to monitor the trial and provide targeted education to the workforce (Fig. 5). “Study” events within the PDSA cycle will occur following the planned interim analyses and as needed based on ad hoc feedback mechanisms that constitute the trial’s QI processes. In addition to declaring superiority, futility, or the need to continue the trial, the PDSA cycles will also focus on documentation of WOB scores and make a determination regarding whether additional education sessions are needed for nurses and respiratory therapists if documentation is infrequent. Figure 6 displays the schedule of trial activities. Protocol changes will be filed with the study institutional review board and the trial registry information will be updated.

**Fig. 5 Fig5:**
[figure not shown]
Plan-do-study-act cycle example that demonstrates how quality improvement methodology is used to support ongoing conduct of the trial

**Fig. 6 Fig6:**
[figure not shown]
Schedule of enrolment, interventions, and assessments

### Dissemination plan

Two manuscripts are planned for the REST EEC trial: (1) this initial description of the study design and statistical analysis plan; (2) reporting the results of the trial. Authorship of the manuscripts will be determined according to guidelines established by the International Committee of Medical Journal Editors [22].

### Trial status

The trial is registered at ClinicalTrials.gov as NCT05909566. The present manuscript describes information contained in the REST EEC Protocol and Statistical Analysis Plan version 1.0, dated December 6, 2023. The “HFNC for Bronchiolitis” PowerPlan went live in CHP Cerner on December 12, 2023. As of January 9, 2024, the PowerPlan has been used 51 times, or an enrollment rate of 1.8/day. Recruitment is expected to continue until approximately January 1, 2026.

## Discussion

There are increasing concerns that the use of HFNC for the management of bronchiolitis in the United States of America is suboptimal, contributing to excess costs and amplifying strains of both personnel and material resources at children’s hospitals during surges of patients afflicted with respiratory viruses [23]. In this context, any effort to safely reduce the utilization of this resource-intensive therapy will be beneficial and will align well with patient-centered outcomes. The REST EEC trial will examine whether CDS supporting standardized HFNC weaning will result in a shorter duration of HFNC among children with bronchiolitis compared to usual care. By randomizing at the level of order placement, as opposed to a quasi-experimental before-after design, the REST EEC trial will more accurately assess for a potential causal relationship between an EHR-embedded HFNC weaning workflow and the duration of HFNC.

As both a demonstration and potential solution to overutilization, single and multicenter de-implementation campaigns have recently worked to reduce the use of HFNC specifically for bronchiolitis, without any reported negative impact on patient care [16, 24, 25]. Importantly, calls for HFNC de-implementation have commonly cited the lack of efficacy data for improving outcomes such as duration of hospitalization or intensive care admission. Constructive opposition has noted that the absence of conclusive data regarding the efficacy of HFNC does not constitute evidence of the magnitude of overutilization of HFNC [26]. Additional data are needed to better understand the impact of HFNC on patient dyspnea, air hunger, agitation, and work of breathing, all of which may be unrelated to the duration of illness or the need for escalation of respiratory support to invasive or noninvasive ventilation. Accordingly, REST EEC examines a potential strategy for more efficient utilization of HFNC while leaving the decision to initiate the therapy to bedside clinicians.

Integrating REST EEC into usual care workflows allows the trial to capitalize on existing care infrastructure, resulting in a more cost-effective deployment. Embedded randomization is a common tactic to optimize software applications in non-healthcare industries but is not yet widely applied in medicine to refine EHR workflows [27]. The insights generated from REST EEC will be rapidly translated into practice, with CDS remaining in place for all children with bronchiolitis if the intervention proves statistically promising compared to usual care and is deemed to be useful by clinicians following review of the final analyses, and the CDS being turned off if there is an insignificant difference in HFNC duration between the intervention and usual care arms. De-implementing ineffective CDS is important for reducing click burdens on frontline staff and mitigating the risk of EHR-associated burnout. REST EEC’s novel, Bayesian design introduces the concept of a posterior probability > 0.8 representing a sufficient threshold to declare a minimal risk intervention superior to the control arm. This full cycle application of Bayesian analysis aligns with the original vision of “evidence-based medicine” described by Dr David Eddy, who coined the term while noting the need for more objective, probabilistic decision-making by physicians that relied on Bayes theorem [28].

HFNC has emerged as a common modality for pediatric respiratory support over the past 2 decades [29]. Its ease of use and noninvasive nature have fostered its adoption as a form of respiratory support; however, the use of HFNC is more resource intensive than other noninvasive methods of respiratory support such as facemasks or low-flow nasal cannula, commonly requiring the expertise of certified respiratory therapists to setup and titrate in the United States of America. REST EEC will help to answer whether standardized HFNC weaning coupled with CDS will result in a shorter duration of HFNC compared to usual care among children with bronchiolitis. Through incorporation of the trial into usual care workflows, relying on QI tools and resources to support trial conduct, and relying on Bayesian inference to determine whether the intervention is superior to usual care, REST EEC is emblematic of a learning health system intervention that blends health system operations with active evidence generation [30].

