### Aim

The objectives of the REST EEC trial are to (1) determine whether a CDS intervention coupled with a clinical effectiveness guideline is effective at reducing the duration of HFNC for bronchiolitis compared with usual care at a large children’s hospital; (2) demonstrate the utility of embedded randomization and associated EHR data analysis for determining whether CDS is a value-added contribution to patient care; and (3) introduce the concept of “statistically promising,” or a posterior probability of ≥ 0.8, as a meaningful Bayesian statistical conclusion for minimal-risk, QI oriented study questions.

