As REST EEC uses an adaptive Bayesian design, virtual trial simulations were conducted to understand statistical design operating characteristics such as sample size, trial duration, and power for putative trial scenarios with a given intervention effect size and to determine feasibility of the planned design. To inform the Bayesian analysis plan, data were extracted from the CHP EDW staged environment, which contained all CHP encounters for the preceding 3 years. Supplemental Table 1 displays the data dictionary used to define the preliminary data to inform simulations. There were 549 encounters that received HFNC with a primary or secondary diagnosis of bronchiolitis. The estimated median time to weaning was 35 h (Fig. 3). Several trial scenarios were explored, with varied accrual rates and effect sizes as measured by the difference in median time to weaning between the CDS intervention arm versus usual care. For each scenario, 5000 virtual trials were simulated and the behavior of each trial was tracked to determine the design operating characteristics. An anticipated effect evidenced by a HR of 1.27, or a 6-h difference between the median time to weaning in the CDS versus usual care arm, was selected as providing a clinically significant but realistic effect of the intervention. HFNC weaning in the CHP PICU commonly occurs following PICU morning rounds. A 6-h decrease in HFNC duration therefore commonly translates into a morning rather than afternoon discharge out of the PICU, which can subsequently facilitate earlier hospital discharge. Three interim analyses (at 12 months, 18 months, and 24 months after study initiation) and one final analysis (at the maximum sample size) will be performed. At each interim analysis, the study will declare superiority of CDS if the posterior probability of HR > 1 exceeds 0.99 or futility of CDS if the posterior probability of HR < 1.15 exceeds 0.8, meaning that futility will be declared if the probability is > 0.8 that the effect of clinical decision support is less than a 4-h reduction in HFNC duration. If neither condition is met, the study will continue to the next interim or final analysis. At the final analysis, CDS will be declared superior if the posterior probability of HR > 1 exceeds 0.9. A clinically actionable posterior probability threshold at which the CDS would be considered “statistically promising” and left in place following trial conclusion was determined to be 0.8 after conferring among the investigators and clinical leadership. Planning for balanced randomization between the CDS intervention and usual care, with a maximum sample size of 350 over approximately 2–3 years (100–150 patients per year), trial simulations indicate there will be a > 0.75 probability of declaring superiority (either interim analysis posterior probability of HR > 1 greater than 0.99 or final analysis posterior probability of HR > 1 greater than 0.9) and a > 0.85 probability of declaring superiority or the CDS intervention showing promise (final analysis posterior probability of HR > 1 greater than 0.8) (Fig. 4). This design was deemed feasible as approximately 150 children with bronchiolitis < 2 years old receive HFNC annually at the study site. Planned secondary analyses include evaluating the primary endpoint among select subgroups, including children treated with beta agonists therapy, children treated for pneumonia, children with complex chronic conditions, children receiving positive pressure ventilation, and children co-diagnosed with croup. The electronic data collection strategy has been designed to encode missing data as absent, avoiding the need for imputation. The primary analysis will be intention to treat (ITT) and a secondary, modified ITT analysis will be performed based on assignments that may have been altered by the ordering clinicians.

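### The Discussion calls a posterior probability above 0.8 enough to declare CDS superior; the analysis section requires 0.9 at the final analysis (0.99 at interims) and treats 0.8 as promising only

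*Protocol article*

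**What the plan says.** **Superiority.** The section on the statistical model, simulation results and analysis plan gives two thresholds. At an interim, "the study will declare superiority of CDS if the posterior probability of HR > 1 exceeds 0.99". At the end, "At the final analysis, CDS will be declared superior if the posterior probability of HR > 1 exceeds 0.9". The interim futility rule is "futility of CDS if the posterior probability of HR < 1.15 exceeds 0.8".

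**Promise.** The same section sets 0.8 as the level at which CDS counts as statistically promising and stays in place after the trial. The Aim presents this category "as a meaningful Bayesian statistical conclusion for minimal-risk, QI oriented study questions", writing it as ≥ 0.8. The Abstract and the Fig. 4 caption keep the two conclusions apart: a probability above 0.75 of superiority, and above 0.85 of superiority or promise. Fig. 4A, according to its caption, shows promising and superior as separate outcomes.

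**Discussion.** Here the design is said to introduce a posterior probability above 0.8 as "representing a sufficient threshold to declare a minimal risk intervention superior to the control arm". The same paragraph keeps CDS in place if the result is statistically promising and clinicians find it useful, with "the CDS being turned off if there is an insignificant difference in HFNC duration between the intervention and usual care arms".

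**The concern.** The Discussion gives a number, uses the plan's own term for its strongest conclusion, and presents the statement as a feature of this trial's design. A reader can fairly take it as the decision rule, so the article prints two thresholds for the primary superiority conclusion.

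The article is the public reference for the later results paper. A final posterior of, say, 0.85 could be reported as superiority with an apparent citation to the protocol, although the analysis section classes it as promising. The stated > 0.75 chance of superiority would then be quoted beside a rule to which it does not belong.

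The turn-off wording adds a second ambiguity. The design has no significance test. Its final categories are superior, promising and inconclusive, with futility at interims. For a posterior between 0.8 and 0.9, *insignificant* read against 0.9 turns CDS off, and read against 0.8 it does not.

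**Working it through.** **1. The texts side by side, for a final posterior P(HR > 1) between 0.8 and 0.9**

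| Place | Label |
|---|---|
| Abstract, Methods | promising, not superior |
| Aim | statistically promising |
| Statistical analysis section | statistically promising; CDS stays |
| Fig. 4 caption | promising, separate from superior |
| Discussion, threshold sentence | superior |

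**2. Inputs from the article.** Maximum 350 patients, 1:1 allocation, 100–150 per year; looks at 12, 18 and 24 months and at 350; N(0, 2.5) prior on log(HR); the thresholds above; target HR 1.27. *Assumptions of this check:* 2.5 is a standard deviation, every patient has an event, accrual is even, and the log(HR) estimate is normal with variance 4/n.

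**3. Which results are in dispute.** At n = 350 the information is 350/4 = 87.5. The prior adds 1/2.5² = 0.16, which is negligible. The standard error is 1/√87.5 = 0.1069.
- Posterior > 0.9 needs log(HR) > 1.2816 × 0.1069 = 0.137, so an estimated HR above about 1.15.
- Posterior > 0.8 needs log(HR) > 0.8416 × 0.1069 = 0.090, so an estimated HR above about 1.09.

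A final estimated HR between about 1.09 and 1.15 would change label.

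**4. Single look.** Power = Φ(ln 1.27 × √87.5 − z), with ln 1.27 × √87.5 = 0.2390 × 9.354 = 2.236.
- 0.9 threshold: Φ(2.236 − 1.282) = 0.830
- 0.8 threshold: Φ(2.236 − 0.842) = 0.918
- At HR = 1, the two rates are 10% and 20%.

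**5. With the interim looks.** Simulation of 1,000,000 trials per cell. At each look the posterior variance is 1/(n/4 + 0.16) and the interim rules apply as written. Looks fall at 100/150/200, 125/188/250 or 150/225/300 patients, then at 350.

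The plan's own figures come first, at HR 1.27:

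| Accrual per year | Superior (final 0.9) | Superior or promising (final 0.8) |
|---|---|---|
| 100 | 0.773 | 0.831 |
| 125 | 0.789 | 0.848 |
| 150 | 0.801 | 0.864 |

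The stated > 0.75 for superiority is reproduced at all three rates. The stated > 0.85 for superiority or promise is reached at 150 per year and missed by up to 2 points at the lower rates, so the approximation is close but not exact.

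At HR = 1, the chance of a result labelled superior:

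| Accrual per year | Final 0.9 | Final 0.8 | Ratio |
|---|---|---|---|
| 100, futility applied | 9.1% | 15.6% | 1.71 |
| 125, futility applied | 9.2% | 15.8% | 1.72 |
| 150, futility applied | 9.4% | 16.4% | 1.74 |
| 100, futility ignored | 10.7% | 20.3% | 1.90 |
| 125, futility ignored | 10.5% | 20.2% | 1.93 |
| 150, futility ignored | 10.3% | 20.1% | 1.96 |

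Interim superiority contributes about 2% in every row and does not depend on the final threshold. The whole rise comes from trials that finish with a posterior between 0.8 and 0.9: with futility applied, 15.6 − 9.1 = 6.5 points at 100 per year and 16.4 − 9.4 = 7.0 points at 150.

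**The case against.** The best defence is that this is one loose sentence in a Discussion. The rule is explicit in the analysis section and repeated in the Abstract and the Fig. 4 caption. The same Discussion paragraph uses *statistically promising* correctly a few lines before. Keeping CDS in place is already tied to 0.8, so the conflict concerns what a result may be called more than what the hospital would do. All of that stands. It shows that the analysis is sound and the repair cheap. It does not remove the second threshold from print.

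Four stronger readings are tempting, and the documents do not support them.
- *The false superiority rate nearly doubles.* That holds only if futility stops are ignored, or for a single look. With the rules as written the factor is about 1.7.
- *The trial will use 0.8 for superiority.* Nothing in the analysis section suggests it. The inflation arises only if the Discussion sentence displaces the stated rule.
- *The plan turns CDS off at a final posterior of 0.8 or less.* The analysis section says when CDS stays, not when it is removed. The Discussion adds that clinicians must find it useful.
- *Null-scenario error rates are missing.* They may be in Fig. 4 or in the full protocol and analysis plan, neither of which can be seen here.

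**Conclusion.** The contradiction is real and rests on the text alone. It concerns the threshold for the trial's main conclusion, so it is more than clerical, although no analysis, sample size, interim rule or power figure needs to change.

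If the Discussion wording governed reporting, a final posterior between 0.8 and 0.9 would be called superiority, and false superiority at HR = 1 would go from about 9% to about 16%. The direction follows from the thresholds. The size depends on the approximation: events in all patients, even accrual of 100–150 per year, futility stops obeyed, and a normal log(HR) in place of the trial's M-spline model.

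The *insignificant difference* wording is a lesser fault in the same paragraph. A reader may take it as plain language for *not promising*, but it does not say so.

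**What to change.** In the Discussion:
1. Describe a final posterior above 0.8 as sufficient to call the intervention statistically promising, and remove the reference to superiority over the control arm. Keep *superior* for > 0.99 at an interim and > 0.9 at the final analysis.
2. Replace *insignificant difference* with the analysis section's posterior-probability categories, and state how these combine with the condition that clinicians find CDS useful. The investigators must settle that rule; the documents do not give it in full.
3. Use one form of the 0.8 boundary throughout. The Aim has ≥ 0.8 and the Abstract, the Fig. 4 caption and the Discussion have > 0.8. The numerical effect is negligible, but the rule should read the same everywhere.

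If null-scenario probabilities for each label are quoted, take them from the trial's own simulations and not from the approximation above.

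The cost is a few sentences, best changed before results are known. No redesign, new data or additional patients are needed.

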## Data Availability

Data and materials are the property of UPMC and the University of Pittsburgh. There is no individual clinical trial participant-level data sharing plan; access is granted for approved use cases only.

## Abbreviations

CDS: Clinical decision support
CHP: UPMC Children’s Hospital of Pittsburgh
EDW: Enterprise data warehouse
EHR: Electronic health record
ETL: Extract, transform, and load
HFNC: High flow nasal cannula
HR: Hazard ratio
PDSA: Plan-do-study-act
PHIS: Pediatric health information systems
PICU: Pediatric intensive care unit
QI: Quality improvement
REST EEC: REspiratory SupporT for Efficient and cost-Effective Care
WOB: Work of breathing
